## Abstract

**Background:**

Both depressive disorder and subclinical depressive symptoms during adolescence are a major public health concern. Therefore, it is important that depression is detected at an early stage and is treated preventively. Prevention based on the principles of Cognitive Behavioural Therapy (CBT) has proven to be the most effective, however research has mainly focused on the effectiveness of “prevention packages” consisting of multiple CBT-components, rather than on the distinct CBT-components. This study will evaluate the relative effectiveness of four core components of CBT (cognitive restructuring (CR), behavioural activation (BA), problem solving (PS) and relaxation (RE)). In addition the relative (cost-)effectiveness of four different sequences of these components will be evaluated: (1) CR – BA – RE – PS, (2) BA – CR – RE – PS, (3) PS – GA – CR – RE and (4) RE – PS – BA – CR.

**Methods:**

We will perform a non-blinded multisite cluster randomized prevention microtrial with four parallel conditions consisting of the four sequences. The four sequences of components will be offered in groups of high school students with elevated depressive symptoms. For each CBT-component a module of three sessions is developed. Assessments will be conducted at baseline, after each CBT-component, prior to each session, at post-intervention and at 6-month follow-up. Potential moderators and mediators will be evaluated exploratively to shed light on for whom the (sequences of) CBT-components are most effective and how effects are mediated.

**Discussion:**

The potential value of the study is insight in the relative effectiveness of the four most commonly used CBT-components and four different sequences, and possible moderators and mediators in the prevention of depression among adolescents. This knowledge can be used to optimize and personalize CBT-programs.

**Trial registration:**

The study is registered in the Dutch Trial Register (Trial NL5584 / NTR6176) on October 13, 2016.

## Background

Depressive disorder during adolescence is a major public health concern, as it is one of the most prevalent mental disorders among adolescents (e.g., [1, 2]). The annual prevalence of major depressive disorder is approximately 7.4% [1]. Lifetime prevalence of depression in adolescents is estimated at 10.6% [1]. These percentages do not even include adolescents with subclinical depressive symptoms. Adolescent depression is associated with a range of adverse consequences such as social isolation [3], poor academic functioning [4], substance abuse [5], suicidal behaviours [6], comorbid psychiatric diagnoses [7, 8] and high societal costs [9]. Not only depressive disorders but also subclinical levels of depressive symptoms put adolescents at risk for poor social and academic functioning [10, 11]. Furthermore, it puts adolescents at risk for subsequent depressive disorders later in life [12]. Therefore, it is important that depression is detected at an early stage and is treated preventively. Programs based on the principles of Cognitive Behavioural Therapy (CBT) have proven to be the most effective and most applied in preventing depression among adolescents (e.g., [13]). Thus far, research has mainly focused on effectiveness of prevention programs as “packages” consisting of multiple CBT-components, rather than on the distinct CBT-components. Little is known about *which* specific components of CBT contribute to the effectiveness of CBT-programs and *in what order* these components should be offered (i.e., what their optimal sequencing is). Most common CBT-components in current prevention programs for depression in adolescents are cognitive restructuring, behavioural activation, problem solving and relaxation (e.g., [14–16]). However, few studies have examined the effectiveness of these specific CBT-components and its sequencing [17]. The planned study is aimed at dismantling the relative effectiveness of core components of CBT and its sequencing in the prevention of depression among adolescents.

Cognitive restructuring is often seen as the fundamental component of CBT. Cognitions play an important role in the theoretical explanation of mood disorders (e.g., [18]). Beck et al. [18] suggested that the way people think and process information in response to stressors, is a primary determinant of mood. In depressed individuals, negative thoughts elicit a depressive mood, while positive thoughts elicit happier moods. Negative thoughts are generated by dysfunctional, negative and often unrealistic beliefs about the self, the world and the future (the cognitive triad). The aim of cognitive restructuring is to challenge these negative beliefs and to generate more realistic thoughts which will help to improve mood [18, 19]. There is debate about the necessity of focusing on cognitions in treating depression in adolescents as their cognitive ability to reflect on their own core beliefs has not yet fully developed (e.g., [20, 21]). This might limit the application of cognitive restructuring in this age group. Yet, there is some evidence for the effectiveness of cognitive restructuring in preventing (and treating) depression among adolescents. A recent meta-analysis showed that preventative and curative CBT including challenging thoughts (which is part of cognitive restructuring) is associated with better outcomes than CBT without this component, but only on the long term [22]. Another meta-analysis showed similar effects of interventions (preventive and curative) emphasizing cognitive change (e.g. CBT and cognitive restructuring treatments) and interventions without cognitive emphasis (e.g. relaxation training) [23].

The CBT-component behavioural activation is theoretically based on behavioural models of depression (e.g., [24, 25]), wherein it is suggested that depression is caused or maintained by a lack of experiencing positive reinforcement from the environment. This may occur because people with depression lack the social skills required to elicit rewarding interactions with others and often show avoidant behaviours [25]. Behavioural activation is aimed at increasing engagement in activities that evoke positive reinforcement [26]. Behavioural activation has proven to be an effective component in preventing (and treating) adolescents’ depression (e.g., [22, 27–31]). For example, the meta-analysis of Oud et al. [22] demonstrated that preventive and curative CBT including behavioural activation (in addition to challenging thoughts, see previous paragraph) resulted in better outcomes on the long term than CBT without behavioural activation. Besides, a Randomized Controlled Trial (RCT) showed that behavioural activation (as a standalone program in only five sessions) was effective in reducing depressive symptoms compared to no treatment in a sample of late adolescents (aged 18–19) [30].

Problem solving refers to the cognitive-behavioural process whereby people attempt to identify or discover adaptive solutions to cope with specific problems arising in daily living [32]. According to D’Zurilla and Goldfried [33] problem solving comprise five different processes, i.e. problem orientation, operationalizing problems/goals, generating solutions, decision making, and implementing and evaluating solutions. Longitudinal studies have shown that deficiencies in any of these processes play a role in the etiology of depression [34, 35]. Problem solving is directed at changing someone’s overall problem-solving orientation, including the accompanying problem-solving techniques [15, 33]. In the context of prevention, problem solving has not (yet) been proven effective. A RCT showed that five weekly sessions of Problem Solving Therapy (provided as guided online self-help) were not more effective in reducing symptoms than a wait list control [36]. However, this result may be due to limitations of the study (e.g., limited power) [36]. It could be expected that problem solving is important in the context of preventing depression among adolescents as adolescence is a challenging and stressful period wherein people are faced with a lot of developmental challenges (e.g., making school/career decisions, developing new friendships, exploring self-identity, achieving autonomy). The component of problem solving focuses on improving problem solving skills to deal effectively with these challenges [37]. In the context of treatment, problem solving has proven to be effective on adolescents’ depression. Kennard et al. [14] showed that CBT including problem solving was associated with better treatment outcomes than CBT without problem solving. Chronically depressed adolescents who received CBT including problem solving were 2.3 times more likely to have a positive response than those who received CBT without problem solving [14].

The CBT-component relaxation is based on the diathesis-stress model for depression [38]. The model states that stress may activate a diathesis or vulnerability, transforming a predisposition for depression into an actual depression [38]. Relaxation is aimed at developing strategies to cope with stress and to reduce its negative effect on a someone’s vulnerability, for example through relaxation exercises [38]. The effect of relaxation techniques on depressive symptoms has rarely been examined in adolescents in both prevention and treatment settings. One study showed equivalent effects of relaxation training and CBT (both 10 sessions) in treating depression among adolescents [39].

Besides the specific components, current CBT-protocols do not have a fixed sequence of components. Even within one session often multiple components are offered (see for example Coping with Depression course for Adolescents (CWD-A), [40]). Nevertheless, patterns can be distinguished. A quick review of four Dutch CBT-protocols (The D(o) epression course (derived from CWD-A), [41]; Pak aan (derived from Taking Action), [42]; Op Volle Kracht (derived from the Penn Resiliency Program), [43]; and Head up, [44]) showed that cognitive restructuring is offered throughout all phases of treatment, while behavioural activation is addressed in the early and middle phase of treatment. The component of problem solving is offered in the middle and final phase, while relaxation techniques are taught in the middle phase. Dobson [19] describes that a typical course of CBT is composed of behavioural activation and problem solving in the early phase of treatment and cognitive restructuring in the middle and final phase. Others suggest that CBT should not consist of a fixed sequence of components, but that the order of components should be based on individual client characteristics and needs [45]. An example of such a personalized modular approach is MATCH-ADTC (Modular Approach to Therapy for Children with Anxiety, Depression, Trauma, or Conduct Problems) by Chorpita and Weisz [46], which allows great flexibility in the sequence of modules (and thus components) based on a flowchart. To the best of our knowledge, no studies investigated whether or not the sequence of CBT-components is relevant for the effect of CBT on depressive symptoms.

In sum, we know that CBT is effective in the prevention of depression among adolescents, but we do not know which components contribute most to its effectiveness and what the optimal sequencing of components is [47]. Therefore, the current study aims to explore (1) the relative effectiveness of the four most commonly used CBT-components in the prevention of depression among adolescents (namely cognitive restructuring (CR), behavioural activation (BA), problem solving (PS) and relaxation (RE)) and (2) the relative (cost-)effectiveness of four sequences of CBT-components. First, we will examine and compare the effectiveness of the four most commonly used CBT-components. We hypothesize that all components are effective on adolescents’ depressive symptoms, but that some components are more effective than others. Because of insufficient evidence, we have no specific assumptions about which components are more effective. Second, we will examine and compare the effectiveness of four sequences of the most commonly used CBT-components. As it is impossible to test all 24 possible combinations because of limited time and budget, we will only investigate the three most logical sequences (condition 1: CR – BA – RE – PS; condition 2: BA – CR – RE – PS; condition 3: PS – GA – CR – RE) and the least logical sequence (condition 4: RE – PS – BA – CR). These four sequences are based on current CBT-protocols, theory and close consultation with mental health professionals. We hypothesize that all sequences are effective on adolescents’ depressive symptoms, but that some sequences are more effective than others. We expect that the conditions 1, 2 and 3 are more effective than condition 4. Furthermore, potential moderators (e.g. severity of depressive symptoms, comorbidity and demographics) and mediators (focusing on the four components namely negative cognitive errors, behavioural activation, problem solving skills and relaxation) will be included to explore for whom and how a component or combination of components works. At last, the role of non-specific treatment variables (client expectancy of treatment, therapeutic alliance, groups cohesion, cooperation with treatment, treatment satisfaction and treatment adherence) will be taken into account.

## Methods

The study methods and results will be reported in accordance with the CONSORT 2010 statement for reporting parallel group randomized trials [48] and the extension to cluster randomized trials [49]. The medical ethics committee CMO Region Utrecht in The Netherlands approved this study (NL59152.041.16). The study is registered in the Dutch Trial Register (Trial NL5584 / NTR6176).

### Design

The study is designed as a non-blinded multisite cluster randomized prevention microtrial with four parallel conditions to evaluate the relative effectiveness of four CBT-components and four different sequences of these components in adolescents at risk of depression. In all conditions an indicated prevention program will be offered consisting of four modules based on the four most commonly used CBT-components (cognitive restructuring (CR), behavioural activation (BA), problem solving (PS) and relaxation (RE)). Each module will consist of three sessions. The sequence of the four modules will differ per condition. The four conditions are shown in Table 1.

**Table 1 Tab1:** Sequence of CBT-modules per condition

	Condition 1	Condition 2	Condition 3	Condition 4
Module 1 (session 1–3)	CR	BA	PS	RE
Module 2 (session 4–6)	BA	CR	BA	PS
Module 3 (session 7–9)	RE	RE	CR	BA
Module 4 (session 10–12)	PS	PS	RE	CR

*Abbreviations. CR* Cognitive restructuring, *BA* Behavioural activation, *PS* Problem solving, *RE* Relaxation

Assessments will be conducted at baseline (*t*_*0*_), during the intervention phase after the first module (after three sessions; *t*_*1*_), during the intervention phase after the second module (after six sessions; *t*_*2*_), during intervention phase after the third module (after nine sessions; *t*_*3*_), at post-intervention (after twelve sessions; *t*_*4*_) and at 6-month follow-up (*t*_*5*_). Additionally, prior to each session, short individual measurements will be administered in order to trace interim effects.

### Participants’ eligibility

Adolescents in all grades of secondary education (from pre-vocational education up to pre-university education) are eligible to participate in the study. Inclusion criteria for the adolescents are (1) aged between 10 and 20 years old, (2) sufficient knowledge of the Dutch language and (3) an elevated level of depressive symptoms at screening, defined as a percentile score of 76 or higher based on the Children’s Depression Inventory-2 (CDI-2; [50]) norm scores (according to gender and age). Exclusion criteria are (1) the absence of adolescents’ or parental consent (for subjects aged younger than 16), (2) currently receiving treatment for mood- or anxiety related problems and (3) suicidal ideation (expressed as a score of 2 (“I want to end my life”) on CDI-2 item 8 followed by a total score of 12 or higher on the suicide items of the Questionnaire assessing Suicide and Self Injury (in Dutch: Vragenlijst over Zelfdoding en Zelfbeschadiging; VOZZ, [51])). Adolescents who are identified with suicidal ideation (at any time point within the study), will be contacted within 48 h and referred to a general practitioner which in turn can refer to mental health care.

In order to minimize the number of false positives, an eligibility check will be conducted at baseline assessment (*t*_*0*_). However, adolescents who do not report an elevated level of depressive symptoms anymore (compared to screening) will not automatically excluded from the study, because of the episodic course of depression. In consultation with the adolescent it will be determined whether or not he/she will participate.

### Recruitment, screening and randomization

Adolescents will be recruited via secondary schools in The Netherlands. All adolescents and their parents (for subjects aged younger than 16) receive written information about the screening and the study. After receiving passive consent, adolescents will be screened with the CDI-2 [50, 52] for depressive symptoms in order to select high-risk adolescents. Students with an elevated level of depressive symptoms will be approached by email and by phone to participate in the study. Written informed consent from adolescents and parents (for subjects aged younger than 16) will be obtained by the first author ([name]) by post or email prior to the initiation of the study. Screening will continue until the planned sample size is achieved (*n* = 256, see subheading ‘sample size’).

Eligible and consenting students from the same school will be stratified by gender (boy or girl) and age (12–13 years, 14–15 years, 16 years or older), because a meta-analytic review found that CBT depression prevention programs showed higher effect sizes for samples with a higher rate of female participants and samples with older participants (> 13.5 years) [53]. Then treatment groups of on average five students (from the same school) will be formed, which are the unit of randomization. The treatment groups will be randomized as a cluster by the first author ([name]), to one of the four conditions, by computer generated block randomization (with a block size of four). Once randomized such a group of students continues as a group receiving the preventive program, with one therapist per group. Blinding of participants is not possible, like in most psychological interventions. However, allocation to the four conditions will be concealed until the introductory meeting, which takes place after the baseline assessment has been completed. The overall study design is shown in Fig. 1**.**

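### The person who obtains consent also randomises the groups, in fixed blocks of four, in an open four-arm trial; if groups are drawn one after another, up to 12 of about 51 allocations are certain to that person beforehand

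*Protocol article*

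**What the plan says.** The Design section calls the study a "non-blinded multisite cluster randomized prevention microtrial with four parallel conditions".

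Under Recruitment, screening and randomization, one person has two tasks. On enrolment: "Written informed consent from adolescents and parents (for subjects aged younger than 16) will be obtained by the first author". On allocation: "The treatment groups will be randomized as a cluster by the first author", and the assignment is "to one of the four conditions, by computer generated block randomization (with a block size of four"). No other block size is given.

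The same section gives the order of steps. Eligible, consenting students of one school are stratified by gender and age, and after that: "Then treatment groups of on average five students (from the same school) will be formed, which are the unit of randomization". On concealment it says that "allocation to the four conditions will be concealed until the introductory meeting, which takes place after the baseline assessment has been completed". It does not say from whom allocation is concealed, who forms the groups, or whether a school's groups are drawn singly or together.

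The Participants' eligibility section adds a discretionary step for students whose symptoms are no longer elevated at baseline (t0): "In consultation with the adolescent it will be determined whether or not he/she will participate". Whether this decision comes before or after the draw is not stated.

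**The concern.** With four arms and blocks of four, each arm occurs exactly once per block. Anyone who knows the first three allocations knows the fourth. The person who runs the draw necessarily knows the past allocations, and that person also deals with students over consent.

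Forming a group before its own draw does not fully protect it. If the next arm is already determined, the make-up of the next group, or the order in which groups are submitted, can be influenced beforehand. The t0 participation decision is open in the same way if it follows the draw.

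The stake is comparability of the arms. Each arm has only about 13 groups and the primary outcome is the adolescent's own CDI-2 report. The Background states an expectation that condition 4 will do worse than the other three. The limitations section already names baseline imbalance as a major risk of the cluster design, and the remedy it offers there is stratification by gender and age.

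**Working it through.** **Inputs (protocol article).** Sample size: d = 0.33, two-sided α = 0.05, power 0.80, baseline–t1 correlation 0.80, icc 0.05, mean cluster size 5, cv 0.30, total 256. Recruitment, screening and randomization: one block size of 4. Design: four conditions. Data analysis: 11 schools included so far.

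**The plan's own figure.** It is not disputed and is used only to count groups.
- n per arm = 2 × (1.96 + 0.84)² × (1 − 0.80²) / 0.33² ≈ 52, as stated.
- Design effect = 1 + ((0.30² + 1) × 5 − 1) × 0.05 = 1.2225, stated as 1.22.
- 52 × 1.2225 = 63.6, rounded up to 64 per arm, 256 in total, as stated.

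**Number of randomised units.** 256 / 5 ≈ 51 groups, or 51 / 4 = 12 complete blocks plus 3 groups. Per arm: 64 / 5 ≈ 13 groups.

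**Scenario A: groups drawn one after another.** The k-th allocation in a block is guessed correctly with probability 1/(5 − k), that is 1/4, 1/3, 1/2 and 1.
- Mean over a block: (1/4 + 1/3 + 1/2 + 1) / 4 = 0.52, against 0.25 by chance.
- Certain allocations: one per complete block, so 12 of 51 = 23.5%.
- Allocations narrowed to two arms: one third position in each of 12 complete blocks and one in the incomplete block, so 13.

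**Scenario B: each school drawn in one batch from one continuing list.** Before the batch is drawn, its first allocation is certain only if the batch starts at position 4. If the four starting positions are taken as equally likely and there are 11 schools, that is 11 / 4 ≈ 3 groups. At 51 / 11 ≈ 4.7 groups per school, blocks of four would not generally line up with schools.

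**Scenario C: each school drawn in one batch that opens its own block.** No allocation is known beforehand: 0 groups.

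**Effect of varying block sizes** (simulation over 51 sequential draws; the observer knows past allocations and the possible sizes, but not the size drawn):

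| Scheme | Certain allocations | Correct-guess rate |
|---|---|---|
| Fixed 4 | 23.5% | about 51% |
| Random 4 or 8 | about 7% | about 48% |
| Random 4, 8 or 12 | about 3% | about 45% |

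**Illustration of size (assumed shift, scenario A).** 12 certain allocations over 4 arms average 3 groups per arm, or 15 of 64 students. If these differed from the other groups by 0.25 to 0.5 SD, the arm mean would move by 15/64 × 0.25 = 0.06 to 15/64 × 0.5 = 0.12 SD before adjustment. That is 18% to 36% of the design effect size of 0.33. The documents give no basis for choosing a value in this range, and zero is possible.

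**The case against.** The strongest reply is that the count depends on an unstated procedure. The described order (stratify the students of one school, form groups, then randomise) fits drawing a school's groups together. In that case the number of predictable allocations is about 3 or none. This stands: the honest range is 0 to 12, and 12 is its upper end.

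The room to steer is also limited. Entry needs a CDI-2 score at or above the 76th percentile, consent comes back by post or email, groups come from one school after stratification, and nobody is named as the one who composes or orders them. This stands too. A reader might infer that a quarter of allocations are in fact known in advance, or that the first author shapes the groups. The article supports neither. It also gives no ground for saying that nothing protects the draw: who holds the list is a detail that an article commonly leaves to the full protocol.

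On impact, the sample size section plans a baseline-adjusted analysis with r = 0.80, and the analysis section adds covariates for demographic variables and depressive symptoms that differ between arms. A shift in measured severity would largely be handled. Differences in motivation or other unmeasured features would not. All arms also receive the same four modules, and the authors state no prior expectation about which component works best. That weakens any motive for the component comparison, but less so for the sequence comparison, where condition 4 is expected to do worse.

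The concealment sentence does not answer the point. It follows directly on the remark about blinding participants, it cannot cover the person who runs the draw, and each earlier allocation is open once that group has had its introductory meeting.

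**Conclusion.** The point holds as a vulnerability. What the article states is enough for it: one person consents and randomises, the only block size equals the number of arms, the trial is open, and the primary outcome is self-reported. If draws are sequential, up to 12 of about 51 allocations are certain to that person and the mean guess rate is 0.52 against 0.25. If a school's groups are drawn together, the number falls to about 3 or to zero. The text does not settle which applies.

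The exposure concerns group composition and order, and the t0 participation decision only if it comes after the draw. Nothing in the article shows that steering occurred, and the planned adjustment leaves only unmeasured imbalance uncorrected. The sample size is unaffected. These counts assume groups of five on average and, for the batch scenario, 11 schools.

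**What to change.** For the remaining schools:

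1. Finalise and lock each school's group lists, including the t0 participation decisions, before any draw.
2. Allocate all groups of that school in one step.
3. Take the allocations from a pre-generated list held by an existing team member who does not recruit or consent students. The article refers to a research team of several members; that one of them is free for this is an assumption.
4. Optionally, use randomly varying blocks of 4 and 8. This cuts certain allocations from about 24% to about 7% under sequential draws but lowers the guess rate only to about 48%, so it supplements steps 1 to 3 and does not replace them. Deleting the block size from the published text would do nothing against the person who runs the draw.

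For groups already allocated, report how and when the draw was done, and whether the t0 decisions came before it. If the draws were already made per school after the lists were fixed, a sentence saying so largely answers the point.

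The cost is one paragraph of protocol text, a new list for the remaining schools and a small logistical change. Arm sizes would be slightly less equal if varying blocks are used.
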